## Abstract

**Background:**

Between 30 and 50% of patients with major depressive disorder (MDD) do not respond sufficiently to antidepressant regimens. The conventional pharmacological treatments predominantly target serotonergic brain signaling but better tools to predict treatment response and identify relevant subgroups of MDD are needed to support individualized and mechanistically targeted treatment strategies. The aim of this study is to investigate antidepressant-free patients with MDD using neuroimaging, electrophysiological, molecular, cognitive, and clinical examinations and evaluate their ability to predict clinical response to SSRI treatment as individual or combined predictors.

**Methods:**

We will include 100 untreated patients with moderate to severe depression (>17 on the Hamilton Depression Rating Scale 17) in a non-randomized open clinical trial. We will collect data from serotonin 4 receptor positron emission tomography (PET) brain scans, functional magnetic resonance imaging (fMRI), electroencephalogram (EEG), cognitive tests, psychometry, and peripheral biomarkers, before (at baseline), during, and after 12 weeks of standard antidepressant treatment. Patients will be treated with escitalopram, and in case of non-response at week 4 or intolerable side effects, offered to switch to a second line treatment with duloxetine. Our primary outcome (treatment response) is assessed using the Hamilton depression rating subscale 6-item scores at week 8, compared to baseline. In a subset of the patients (n = ~40), we will re-assess the neurobiological response (using PET, fMRI, and EEG) 8 weeks after initiated pharmacological antidepressant treatment, to map neurobiological signatures of treatment responses. Data from matched controls will either be collected or is already available from other cohorts.

**Discussion:**

The extensive investigational program with follow-up in this large cohort of participants provides a unique possibility to (a) uncover potential biomarkers for antidepressant treatment response, (b) apply the findings for future stratification of MDD, (c) advance the understanding of pathophysiological underpinnings of MDD, and (d) uncover how putative biomarkers change in response to 8 weeks of pharmacological antidepressant treatment. Our data can pave the way for a precision medicine approach for optimized treatment of MDD and also provides a resource for future research and data sharing.

**Clinical Trial Registration:**

The study was registered at clinicaltrials.gov prior to initiation (NCT02869035; 08.16.2016, URL: https://clinicaltrials.gov/ct2/results?cond=&term=NCT02869035&cntry=&state=&city=&dist=)

## Introduction

Major Depressive Disorder (MDD) is one of the most severe and common brain disorders worldwide with a huge impact on life quality and socioeconomic status (1, 2). It has been linked to serotonergic dysfunction, cognitive disturbances, brain network dysfunction, vulnerability to stress, neuro-inflammation, and gene by environment factors. Still, the understanding of the pathogenesis remains limited. Guidelines for MDD treatment selection are still predominantly based on simple clinical observations about overall MDD severity, and in the case of recurrent depressive episodes, it is also based on personal patient history of treatment responses. Conventional medical treatment is mainly based on intervention of the monoaminergic system in the brain, in particular the serotonin (5-HT) system. Selective serotonin reuptake inhibitors (SSRIs) act through blockage and subsequent downregulation of the serotonin transporter (SERT) (3), which presumably induces increased extracellular 5-HT levels. However, robust evidence for a central 5-HT hypofunction in patients with MDD *in vivo* is lacking (4). Roughly one third of patients suffering from MDD do not respond sufficiently to 5-HT acting drugs (5, 6), suggesting a diverse pathophysiology. The diagnostic criteria for MDD may cover a heterogenous collection of various biological entities and consequently, it is not surprising that a “one size fits all” treatment strategy is suboptimal (7). Currently, the time from starting to administer a potentially efficacious drug until it can be determined if the clinical response is satisfactory is, at best, 4–6 weeks. In clinical practice, the lack of convenient and accurate tools (e.g., quantitative and/or biological) to predict treatment response prolongs the delay from diagnosis to effective treatment and constitutes a major challenge for both clinicians and patients. Therefore, stratification of subtypes and a shift toward precision medicine, e.g., through identification of predictors of treatment response, so-called biomarker(s) that can help optimize treatment choice, is of paramount importance. Candidate biomarkers could be related to neurotransmission, specific neural networks or structural alterations in specific brain regions that can be detected by brain imaging modalities such as positron emission tomography (PET), functional magnetic resonance imaging (fMRI), and electroencephalogram (EEG) or altered biophysiological or cognitive functions (4, 8). It has also been suggested that rather than a single biomarker, an algorithm involving a set of biomarkers may prove useful to subgroup patients and predict their response to certain treatment strategies in MDD (9). Several biomarkers derived from prior large studies such as iSPOT-D, EMBARC, and CANBIND for prediction of drug response in MDD have been proposed (10–12). Here, we use multimodalities (PET, fMRI, and EEG, cognitive testing, psychometrics, and peripheral biomarkers) as part of a deep phenotyping and as a unique feature to our trial, we study modes of action in the brain on a neurotransmitter level. Thus, our trial contributes with novel insights as well as provide a dataset for cross-validation of other identified predictors of psychopharmacological antidepressant treatment response. In a non-randomized, longitudinal, open clinical trial, patients with moderate to severe depression will be treated with SSRI following Danish guidelines. In order to map neurobiological signatures of treatment, we will re-examine a subset of the cohort with neuroimaging and EEG after 8 weeks of SSRI treatment and assess cognitive changes after 12 weeks. This clinical trial is part of a larger research initiative, “NeuroPharm”, which addresses pertinent and basic questions regarding human brain disease mechanisms and seeks to predict brain responses to categories of neuro-modulatory interventions as well as treatment efficacy (www.np.nru.dk). We anticipate that this study will critically advance and inform future stratification strategies, further uncover pathophysiological and treatment mechanisms and, hopefully, guide future precision medicine approaches to optimize treatment strategies for patients suffering from MDD.

Imaging techniques have vastly increased our understanding of the underpinning cerebral mechanisms involved in MDD (13). Serotonergic dysfunction is considered a central mechanism in depression, and a recent review points at the 5-HT 4 receptor (5-HT_4_R) as highly implicated in MDD (14). For example, 5-HT_4_R agonism has shown rapid antidepressant -like behavioral effects in rodents (15), and experimental models suggest that cerebral 5-HT_4_R levels are sensitive to central 5-HT modulation in rodents (16, 17). Subsequent clinical studies from our group demonstrated that cerebral 5-HT levels can be indexed in an inverse manner through molecular brain imaging of the 5-HT_4_R by using the PET-ligand 11C-SB207145 *in vivo* (18). We here aim to evaluate 5-HT_4_R binding as a candidate predictor of antidepressant response to drugs targeting the 5-HT system in the hitherto largest cohort of MDD patients with PET brain imaging of serotonergic markers. We hypothesize that 1) patients with MDD differ in cerebral [^11^C]SB207145 binding at baseline compared to healthy controls; 2) [^11^C]SB207145 binding at baseline in patients with MDD predicts remission after 8 weeks of pharmacological serotonergic intervention; 3) After 8 weeks of serotonergic intervention, patients with remitter status have a significantly greater reduction in cerebral [^11^C]SB207145 binding than non-responders. For an overview of primary hypotheses for other modalities, see **Appendix 1**.

fMRI can be used to assess regional activity and resting state functional networks in MDD. One systematic review found abnormal (negative bias) reactivity in amygdala responsiveness to facial expressions and emotional stimulation in patients with MDD versus healthy controls (19), and pre-treatment low amygdala reactivity has shown to be predictive for antidepressant treatment response (20). A study with 70 patients with MDD was able to predict treatment recovery with ~80%, by investigating amygdala reactivity to facial emotions and its interaction with history of early life stress (21). Another study from our group showed that amygdala reactivity was associated with brain 5-HT_4_R binding and hence putatively extra synaptic 5-HT levels in healthy individuals. This established a plausible connection between 5-HT levels and amygdala activation, both involved in emotional cognitive processes (22). This exemplifies how a multimodal PET and fMRI strategy can highlight molecular mechanisms mediating drug effects on brain function (23). Resting state fMRI (rs-fMRI) measures fluctuations in fMRI signal during the absence of an explicit task and is widely used to assess distributed intrinsic networks such as the “default mode network” (24). Alterations in rs-fMRI connectivity have been described in MDD (25) and a recent study suggested that rs-fMRI can define subtypes of MDD and predict antidepressant treatment response (26), but this has been contested by others (27). Although promising, brain imaging studies have in general been inconclusive and with small sample sizes (9, 28). In the current trial, we will use task-based and rs-fMRI in a large cohort of patients with MDD and investigate the association between 5-HT_4_R levels (as a proxy for brain serotonin levels) and the clinical outcome of SSRI treatment.

EEG, a monitoring technique for direct ongoing neural activity, has been reported to be associated with treatment response in MDD [see, e.g., review (29)]. Prior studies have found that treatment responders have higher cortical alpha activity (30) and higher theta activity at rostral anterior cingulate cortex compared to treatment non-responders (31, 32). Of note, these biomarkers were derived from the resting EEG data, which is relatively easy to implement in the clinic. Furthermore, earlier evidence from event-related-potential (ERP) studies have suggested that ERP biomarkers such as auditory P300 (a positive waveform around 300 ms after stimulus onset) and loudness-dependence of auditory evoked potentials (LDAEP) can be predict drug treatment response (33, 34), and are linked to the serotonergic transmitter system (35). In the current trial, the predictive values of pretreatment EEG/ERP biomarkers will be examined.

Disturbances in cognitive processes including memory, attention, and executive functions are commonly reported in MDD (36) and contribute to psychosocial impairment and workforce disability (37). In addition, affective bias in information processing (i.e., favoring negative information over positive information at different levels of information processing) has been proposed as a central mechanism in the development and maintenance of depressive symptoms (38) which is also predictive of later treatment response to antidepressant drugs (39). Notably, cognitive disturbances do not always resolve with the remission of a depressive episode, suggesting a dissociation between core mood and cognitive symptoms in MDD (40). Combined with the low cost and relative ease of testing in a clinical setting, this distinguishes cognitive disturbances as a promising marker for stratification of depression subtypes as well as an important target for antidepressant treatment. In the present study, we therefore aim to map a broad range of cognitive disturbances in MDD, including both cold (non-emotional) and hot (emotional) cognitive processes, and explore whether they may be used to characterize clinically relevant subgroups in MDD. Based on earlier observations in healthy individuals, we expect memory performance to map onto hippocampal 5-HT_4_R availability (41) and possibly affective bias in verbal memory in MDD (42).

Evidence of inflammation-associated MDD has emerged over the years (43). Patients with MDD show elevated levels of inflammatory markers in peripheral blood (44) which may affect treatment response such that higher levels are associated with worse response (45). It has also been suggested that patients with MDD have higher levels of activated microglia, as illuminated with PET (46). Proinflammatory cytokines may influence the 5-HT homeostasis in the brain by acutely upregulate SERT through intercellular pathways (i.e., linked to p38 mitogen-activated protein kinase) and presumably thereby reduce synaptic 5-HT levels (47). Interestingly, cognitive dysfunction, a prevalent symptom in depression, also appear to be linked to an inflammatory response (48). We here aim to determine if higher levels of systemic inflammatory markers are associated with 5-HT_4_R brain binding, depression status at baseline and clinical treatment response.

Another area of interest is the association between MDD and signatures of early aging. There is an increased mortality and prevalence of age-related diseases in recurrent depression (49, 50). Oxidative stress on nucleic acids is a general element of aging and has been suggested to be an underlying biological mechanism of the accelerated aging observed in depression (51). Previous research from our group has found evidence for such a link, both in studies of psychological/biological stress and oxidative stress in patients and in rodent models of depression (52–54). Earlier findings indicate alterations in levels of oxidative stress during antidepressant treatment and it is hypothesized that treatment response is related to a transient increase in oxidative stress levels, perhaps due to neurotrophic processes and/or peripheral changes in energy metabolism (55–57). Urinary 8-oxodG and 8-oxoGuo are sensitive and specific markers for systemic DNA/RNA damage from oxidation (58). We here aim to investigate urinary 8-oxodG and 8-oxoGuo as a predictive biomarker for antidepressant treatment response, its association with changes in psychopathology, structural and functional brain changes, and markers of psychological and biological stress. Additionally, we will investigate whether hormonal [estradiol, testosterone, progesterone and follicle-stimulating hormone (in females)] and metabolic status can predict antidepressant treatment response and explore whether these associations are related to genetic make-up (specified below), psychopathology and the occurrence of early life stress using self-reported childhood adverse events and parental bonding quality questionnaires, which also may interact with the 5-HT system (59, 60).

Sexual dysfunction (e.g., low sexual desire, arousal difficulties, and anorgasmia) is a prominent feature of MDD, which often leads to a decline in quality of life (61, 62). Lack of interest to what is usually pleasurable, i.e., anhedonia, is a core symptom in MDD and may also be reflected in reduced sexual desire/interest. Sexual dysfunction, in particular anorgasmia and sexual arousal difficulties may further be linked to serotonergic dysfunctions (63) as seen in MDD. As a complicating factor, impaired sexual health related to MDD may worsen with antidepressant treatments targeting the 5-HT system. For example, in a group of 704 patients with MDD treated with an antidepressant drug (SSRI) or serotonin-norepinephrine reuptake inhibitor, about half of them developed or experienced worsening in their decreased sexual desire as a side-effect, which was also associated with reduced quality of life, lower self-esteem and adverse effects on mood and partner relations (62). We currently do not know which patient characteristics predict sexual dysfunction in response to SSRI treatment. However, differences in individual serotonergic brain architecture and/or serotonergic response to antidepressant treatment (e.g., SSRI) may play a role. In this study, we aim to map the frequency and predictors of SSRI induced sexual dysfunction and determine if serotonergic tonus (measured by 5-HT_4_R PET binding) pre-treatment, or changes in response to SRRI treatment, is associated with sexual desire and/or development of SSRI-induced sexual dysfunction in MDD.

Previous findings from our group have repeatedly demonstrated a coupling between key features of the 5-HT system and hypothalamus- pituitary- adrenal axis (HPA-axis), which regulates the release of the stress-hormone cortisol (64). Such HPA-axis dynamics can be measured by the cortisol awakening response. Our results support that both serotonin transporter availability (65), and serotonergic tone or direct capacity for 5-HT_4_R agonism (64) support a healthy cortisol response to HPA-axis stimuli. A well-functioning and dynamic HPA-axis is critical for coping with everyday life stressors, and HPA-axis dysregulation is a prominent feature of MDD. Although heightened CAR is associated with relapse of depressive episodes in patients with a history of depression (66), in the more advanced depressed stages, i.e., chronic depression, HPA-axis dynamics are blunted as opposed to recent-onset depression (67). Notably, normalization of the HPA-axis in response to SSRI treatment appears to protect against relapse (68). Thus, the SSRI treatment response is likely to depend on restoring HPA-axis dynamics at least in a subgroup of MDD patients. In this trial, we will assess CAR in patients with MDD, the effect of SSRIs on CAR, investigate its association with baseline 5-HT_4_R distribution, as well as evaluate CAR as a predictor of antidepressant treatment outcome.

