##### Clinical Procedure After Treatment Initiation

After completion of baseline examinations, patients will receive flexible doses of the SSRI drug escitalopram, initially 5 mg for 3–5 days depending on side effects (e.g., nausea), followed by 10 mg daily until their first follow-up visit and further adjusted individually to a maximum dose of 20 mg. Escitalopram was chosen as it binds with high selectivity to the 5-HT transporter and has minimal affinity for other receptors (74). Patients are allowed short-time treatment with cyclopyrrolone (a nonbenzodiazepine hypnotic agent) or oxazepam (a benzodiazepine) to reduce anxiety and sleep disturbances which may be prominent in the initial treatment phase and have shown not to influence treatment continuation (75), but all are requested to avoid use 3 days prior to brain scans. Clinical follow-up sessions with a study physician or trained research assistant are scheduled in an out-patient clinical setting after 1, 2, 4, 8 and 12 weeks of treatment to evaluate treatment response and side effects. Visits can deviate a maximum of one week from the original time scheduled. No cognitive behavioral therapy or other psychotherapy program is provided during clinical visits. No treatment (pharmacological or psychotherapeutically) other than the medical monotherapy provided in this study is allowed elsewhere during the trial. At week 4, early non-responders (see definition below) or patients with unacceptable side effects are offered to switch to a standard second line antidepressant treatment; duloxetine (individually adjusted doses of 30–120 mg per day), which is a serotonin-norepinephrine reuptake inhibitor. Duloxetine was chosen according to clinical guidelines for second line antidepressant treatments. Cerebral 5-HT_4_R binding in humans is unaltered by injection of escitalopram (76). No prior *in vivo* studies have investigated the effect of duloxetine on 5-HT_4_R binding in the human brain, but *in vitro* work has shown that duloxetine has negligible affinity for the 5-HT_4_R (77). That is, none of the pharmacological compounds directly target 5-HT_4_R’s. The week 4 timepoint is in line with national guidelines in Denmark for switching to a second-line antidepressant treatment (4–6 weeks). Since our cohort receives frequent clinical follow-up sessions, patients can reach max dose of escitalopram (20 mg daily) already after 2 weeks. As such, switching after 4 weeks is considered appropriate for early non-responders in this trial set-up. All antidepressant medicine will be provided for free to improve compliance. Compliance will be assessed by serum escitalopram/duloxetine blood tests after eight weeks of treatment as well as tablet count at each follow-up. At each visit, depressive symptoms are rated using the HAMD_17_ and the HAMD_6_ subscale. HAMD_6_ captures core symptoms of depression more directly (and disregards sleeping quality), and has been found to be sensitive to antidepressant treatment response (69). Potential side effects due to intervention will be monitored at each visit using the “Udvalg for Kliniske Undersøgelser” scale (78). To ensure agreement and allow alignment of ratings, HAMD_17/_HAMD_6_ co-ratings between all the clinical investigators will be performed regularly during data collection. A maximum of 20% deviation from the “gold-standard” chief psychiatrist is allowed, or else a new satisfactory co-rating is needed before independent rating of study participants.

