
##### Clinical Response Status

###### Primary Clinical Outcome Measure

The primary outcome measure is categorical and built to capture patients with an early as well as sustained, either excellent or poor response to treatment. Patients are classified as either “remitters”, “non-responders”, or “intermediate responders” after 8 weeks of treatment. These categories are based on percentage changes of depressive symptoms from baseline, as measured by HAMD_6_. Remitters must have ≥50% reduction in HAMD_6_ at 4 weeks (early responders) and a HAMD_6_ score <5 after 8 weeks of treatment. Non-responders have <25% reduction in HAMD_6_ after 4 weeks (early non-responder) and <50% reduction in HAMD_6_ after 8 weeks of treatment. Patients who do not meet the criteria above are defined as “intermediate responders” at week 8. The primary predictor analyses are directed to predict treatment response in a binary fashion (either remitter or non-responder (see **Figure 3**).

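### Hypothesis 3 mixes response with drug and time on drug, because the week-4 cut that triggers the duloxetine offer is also part of the non-responder definition; the SSRI label on the week-8 outcome needs reconciling

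*Protocol article*

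**What the plan says.** All references are to the protocol article.

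- **Hypothesis 3** (Introduction): after 8 weeks of serotonergic intervention, "patients with remitter status have a significantly greater reduction in cerebral [^11^C]SB207145 binding than non-responders".
- **The switch** (Clinical Procedure After Treatment Initiation): "early non-responders (see definition below) or patients with unacceptable side effects are offered to switch to a standard second line antidepressant treatment; duloxetine". It is an offer; expected uptake is not given.
- **Response groups** (Primary Clinical Outcome Measure): "Non-responders have <25% reduction in HAMD_6_ after 4 weeks (early non-responder) and <50% reduction in HAMD_6_ after 8 weeks of treatment". "Remitters must have ≥50% reduction in HAMD_6_ at 4 weeks (early responders) and a HAMD_6_ score <5 after 8 weeks of treatment". "Patients who do not meet the criteria above are defined as “intermediate responders” at week 8".
- **Who is rescanned** (Materials and Methods, opening paragraph): about 40 patients across the whole range of response, with no restriction by drug.
- **Who is analysed, with which covariates** (Statistical Analyses): serum limits for verified compliance are set for both drugs, so a duloxetine user counts as compliant. The named covariates are age, sex and modality-specific ones, with 5-HTTLPR as the example for 5-HT4R.
- **The two drugs and the PET signal** (Clinical Procedure): the article argues that neither drug acts directly on the receptor, and concedes that "No prior *in vivo* studies have investigated the effect of duloxetine on 5-HT_4_R binding in the human brain".
- **The target**: the Abstract's aim is to "evaluate their ability to predict clinical response to SSRI treatment as individual or combined predictors", and the Introduction also describes the rescan exposure and the clinical outcome as SSRI treatment. Hypotheses 2 and 3 speak of serotonergic intervention, and the Discussion of standard treatment.

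**The concern.** The switch rule and the response definition share one week-4 cut, so drug exposure at the rescan is tied to response group by design. Remitters will mostly be rescanned after about 8 weeks of escitalopram. Non-responders who accepted the switch will be rescanned after about 4 weeks of each drug. A difference in binding change between the groups could then reflect response, drug, time on drug, or a mixture of these.

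The absence of direct receptor affinity does not settle this. The Introduction reads 5-HT4R binding as an inverse index of cerebral serotonin. An indirect difference between drugs, or between exposure times, is the kind of signal that such an index would pick up.

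The second issue concerns the target. Week-8 status, and the continuous week-8 change, measure response to escitalopram with optional duloxetine. An early non-responder to escitalopram who reaches at least 50% reduction by week 8 after switching becomes an intermediate responder and leaves the binary comparison. A result on that outcome is a result about the regimen, and calling it SSRI response says more than was measured.

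**Working it through.** **1. The structural link, from the definitions**

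| Group | HAMD6 reduction at week 4 | Route to duloxetine | In the binary contrast? |
|---|---|---|---|
| Remitter | ≥50% | side effects only | yes |
| Non-responder | <25% | early non-response (side effects possible too) | yes |
| Early non-responder who reaches ≥50% at week 8 | <25% | early non-response | no (intermediate) |

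**2. The nearest stated figure.** The article gives 80% power at about 40 rescans for the association of BP_ND change with HAMD6 change. With two-sided α = 0.05 (assumed; none is stated), Fisher's z gives the correlation needed: r = tanh[(1.960 + 0.842)/√(40 − 3)] = tanh(0.461) = 0.43. No slope, correlation or HAMD6 SD is given, so the 80% can be neither confirmed nor refuted. It concerns the continuous association and not the group contrast of hypothesis 3.

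**3. Bias in the group contrast.** Let f and g be the shares of rescanned non-responders and remitters on duloxetine, and δ the between-drug difference in log BP_ND change. With no true response effect, the expected group difference is

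bias = (f − g) × δ.

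Inputs:
- SD of log change 0.08: from the article, held fixed as the total SD.
- 13 vs 13: assumed, a third of 40 in each extreme group.
- f = 0.5 to 0.7, g = 0, and δ: assumed.

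SE = 0.08 × √(1/13 + 1/13) = 0.0314. The rejection rate comes from the noncentral t distribution with 24 df and noncentrality bias/SE.

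| δ | bias, f = 0.5 | error rate | bias, f = 0.7 | error rate |
|---|---|---|---|---|
| 0 | 0 | 5.0% | 0 | 5.0% |
| 0.02 | 0.010 | 6.1% | 0.014 | 7.1% |
| 0.04 | 0.020 | 9.4% | 0.028 | 13.7% |
| 0.08 | 0.040 | 23.2% | 0.056 | 40.3% |

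For scale, the article takes 8% as the effect of fluoxetine on this binding. The bottom row therefore assumes that the drugs differ by about one whole SSRI effect, and δ = 0.04 by about half of one.

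**4. Direction.** If binding falls less in patients switched to duloxetine, the bias favours hypothesis 3. If it falls more, the bias works against it. The article gives no basis for choosing.

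**5. Cost of adjusting for drug.** With all remitters on escitalopram, the adjusted group effect rests on the unswitched non-responders. Its variance relative to the unadjusted contrast is

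[1/13 + 1/(13(1 − f))] / (2/13).

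This is 1.5 at f = 0.5 and 2.2 at f = 0.7. At f = 1 the group effect cannot be estimated.

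**6. Baseline predictors.** The switch comes after the baseline measurement, so drug cannot confound a baseline biomarker's association with outcome. What the switch changes is the outcome being predicted.

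**The case against.** The strongest defence has four parts.

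- *The wider target is already stated.* Hypotheses 2 and 3 name serotonergic intervention, the Discussion names standard treatment, and the Abstract discloses the switch. This stands for those passages and reduces the target issue to inconsistent labelling.
- *Drug may yet be a covariate.* The phrase on modality-specific covariates could include it in an analysis plan that is not shown. This is possible, but it would not remove the overlap that the article itself fixes between the switch rule and the non-responder definition.
- *The continuous analysis covers everyone.* Intermediate responders stay in the secondary analysis, and the rescan power was stated for it. That is true, but it mixes drugs in the same way.
- *The remedies are imperfect.* Drug at rescan is itself a consequence of week-4 response, and restricting to escitalopram selects on early response. This stands, and is why they belong as sensitivity analyses.

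A reader might also infer more than the article supports:

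- That the switch is offered to exactly the non-responder group. Side-effect patients are offered it too, and some early non-responders end as intermediate.
- That most non-responders took duloxetine, or that those left in the group failed both drugs. An offer is not uptake, and anyone who declined has failed only escitalopram.
- That baseline prediction is confounded by drug. It is not.
- That a definite amount of power is lost because switched patients become intermediate. Neither uptake nor improvement after switching is given, and some of those patients might have improved on escitalopram anyway.

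**Conclusion.** The point holds for hypothesis 3. By the article's own definitions, eligibility for the switch is tied to response group, switchers remain in the analysis, and drug is not a named covariate. As written, a remitter versus non-responder difference in binding change cannot be attributed to response alone.

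How much this matters cannot be determined from the article. The error rates of about 6–7%, 9–14% and 23–40% illustrate between-drug differences of 0.02, 0.04 and 0.08. They rest on assumed group sizes and uptake, no remitter on duloxetine, and a simple t-test in place of the planned latent variable model. With no between-drug difference there is no bias, and the article cannot exclude one.

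For the baseline predictors the conclusion is narrower: the outcome is valid for the regimen given, but the SSRI label in the Abstract and Introduction does not match it.

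**What to change.** No change to patient care is needed.

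1. **Hypothesis 3.** Keep the planned contrast. Report drug at rescan by response group. Prespecify a sensitivity analysis of BP_ND change against continuous HAMD6 change in patients on escitalopram throughout, with a drug-adjusted model in the full rescan group as support. Attribute a group difference to response only if these agree with the main contrast.
2. **Target.** Reconcile the SSRI wording with the regimen actually given. Back any claim specific to SSRI response with a sensitivity analysis based on week-4, pre-switch response, applied to all patients alike so that accepting or declining the offer does not alter the classification.

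**Cost.** This needs analysis and reporting text but no new data. The escitalopram-only analysis uses fewer scans and loses much of the poor-response end. Drug adjustment raises the variance of the group contrast by a factor of about 1.5 to 2.2 under the assumptions above, and fails if every rescanned non-responder switched. Both should therefore supplement the planned test and not replace it.
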